### Statistical methods

Team and patient outcomes will be compared on an intent-to-treat basis.

#### Readmission

Two patient follow-up periods will be investigated for unplanned hospital readmission: the primary outcome, 30 days post-discharge, and a secondary outcome period of seven days post-discharge. Discharge records will be examined for patients discharged to home between one week after intervention period commencement and one month after intervention conclusion. Readmission proportions will be calculated for patients discharged from intervention and control group teams. The significance of the difference in proportions will be tested with chi-square and association statistics adjusted for the cluster randomized design [29-32]. The primary aim of the trial is to estimate the population-level intervention effect on binary-coded readmission outcomes; consequently, generalized estimating equations will be employed to control for clustering.

Some patients could have multiple hospital admissions, possibly to different hospitals during the study period. Furthermore, some of the admissions may qualify as an "outcome" while others do not. This situation raises a possibility that patients could change clusters (teams) during the trial, by being readmitted to a different GIM team within the same hospital that discharged them earlier in the intervention period. Therefore, a patient will contribute an observation to the analysis only from their first admission during the intervention period. If the readmission is to a different hospital than the index admission, then the readmission is 'credited' to the hospital of the index admission.

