### Outcomes: measurement

#### Readmission data

The Discharge Abstract Database (DAD) is managed by the Canadian Institute for Health Information. The DAD contains demographic, diagnostic, procedural and hospitalization data on hospital discharges (i.e., inpatient, acute, chronic, rehabilitation) and day surgeries in Canada. Data in the DAD can be used to identify dates of index hospital admissions and, subsequently, readmissions. A subset of the DAD relating to Ontario hospital admissions is held at the Institute for Clinical Evaluative Sciences (ICES) in Toronto, Ontario. ICES is an independent, non-profit organization with a core mission to conduct research that contributes to the effectiveness, quality, equity and efficiency of health care and health services in Ontario.

To develop a data file of hospital readmissions among patients discharged from CTTs participating in the SCRIPT Programme, we will use information in the DAD to establish a link between patients and the team that treated them. The key to using this method successfully lies in our identification of a patient's most-responsible physician. In Ontario, all practicing physicians are required to register with the province's regulatory body, the College of Physicians and Surgeons of Ontario (the CPSO). The CPSO assigns every registered physician a unique registration number. This number is a data field in the DAD; it appears on a discharged patient's record line. It is also publicly available with the physician's name on the Internet site of the CPSO.

Leaders of GIM divisions will provide us with the names and team assignments of physicians who were on rotation in GIM CTTs during SCRIPT's intervention periods. When we know a physician's name from GIM records, we can search for his or her profile in the CPSO Internet site. Physicians' CPSO registration numbers will serve as the link between their positions in GIM CTTs and discharge information in the DAD. We will compile a list of registration numbers of physicians who served in GIM during the study period, submit the list to database managers at ICES, and obtain a data set containing de-identified records of patients treated by a physician who served in GIM during the SCRIPT intervention period. In this way we will be able to determine the CTT where a patient received treatment.

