#### Prescription drug therapy

We will examine an outcome measure originating in the evidence-based medicine paradigm. Clinical evidence-based guidelines exist [26] to support appropriate uses of drugs for treatment of diseases commonly seen in GIM patients: diabetes, community acquired pneumonia, congestive heart failure, hypertension, asthma, chronic obstructive pulmonary disorder, stroke, and acute myocardial infarction. A database exists that can be used for investigation of adherence to evidence-based prescribing practices. This database is used in the Ontario Drug Benefit (ODB) program.

For defined groups of individuals, the Ontario Ministry of Health and Long-Term Care covers most of the cost of prescription drug products listed in the ODB formulary. Importantly for our purposes, one of these groups is Ontario residents 65 years of age and older. For drug products prescribed by an authorized Ontario prescriber, the ODB program covers approximately 3,000 prescription drug products.

The ODB program pays for listed drug products for individuals eligible for ODB coverage if the drugs are purchased in an Ontario pharmacy that is on-line with the ministry's Health Network or from an Ontario doctor licensed to sell prescription drug products. In 2004–2005, 70% of ODB beneficiaries were age 65 or older. It is likely that a majority of patients admitted into and discharged from GIM wards in the participating hospital sites are in this age group. We believe that many are eligible beneficiaries under the ODB program and that a large share of their post-65 prescription drug use history will exist in databases of the ODB program.

For analyses of prescription drug therapy, subjects are patients who are admitted to GIM divisions of participating hospital sites on or after the start date of the intervention at the site, and who are discharged to home from the GIM division on or before the last day of the next full month that follows the conclusion date of the intervention period. We will construct an ODB record for these patients that extends for 60 days after their date of discharge.

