### Sample size

Sample size and power were estimated with PASS software [27]. The trial's primary outcome is the proportion of unplanned hospital readmissions among patients discharged from a GIM team. We assume an intracluster correlation coefficient of 0.01. In this trial we expect there will be in excess of 200 patients admitted into each clinical teaching team in the 2-month intervention period. In total there will about 4000 patients admitted into and discharged from twenty clusters (teams) over five hospital sites. We assume that a typical rate of readmission among GIM patients within 30 days after discharge is ten percent. When significance is set at p < 0.05, the trial would have 93% power to detect a 5.0 percentage-point lower rate of unplanned hospital readmission among patients discharged from intervention CTTs than control CTTs (i.e., 10% versus 5%). A 5.0 percentage-point difference would represent a fifty-percent difference in readmission rates between intervention and control team patients.

If the rate of readmission within 30 days of discharge from GIM treatment is five percent, and if the intracluster correlation coefficient is 0.01, then the trial has 67% power to detect a 2.5 percentage-point lower rate of readmission among patients discharged from intervention teams. Again, this is a fifty-percent difference (i.e., 5% versus 2.5%).

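### The primary cohort is selected by discharge date, with no single admission window and a physician roster that may stop before the last eligible discharge; an admission-date index would fix this cheaply

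*Protocol article*

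**What the plan says.** All references are to the protocol article.

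- **Statistical methods, Readmission, first paragraph:** "Discharge records will be examined for patients discharged to home between one week after intervention period commencement and one month after intervention conclusion". This bounds the discharge date only.
- **Same section, second paragraph**, after discussing repeat admissions and patients who change teams: "a patient will contribute an observation to the analysis only from their first admission during the intervention period". This ties the index admission to the intervention period.
- **Sample size:** "The trial's primary outcome is the proportion of unplanned hospital readmissions among patients discharged from a GIM team". The power calculation expects "in excess of 200 patients admitted into each clinical teaching team in the 2-month intervention period", in total "about 4000 patients admitted into and discharged from twenty clusters (teams) over five hospital sites".
- **Outcomes: measurement, Readmission data:** the link from patient to team is the registration number of the most responsible physician. Division leaders supply the "names and team assignments of physicians who were on rotation in GIM CTTs during" the trial's intervention periods. The list of numbers is then described as covering the study period, and the resulting data set as covering the intervention period again.
- **Outcomes: measurement, Length of stay data:** built by the same process as the readmission data. Hypothesis 3 expects shorter stays in intervention teams.
- **Outcomes: measurement, Prescription drug therapy:** patients admitted on or after the site's start date and "discharged to home from the GIM division on or before the last day of the next full month that follows the conclusion date" (here, the end of the site's intervention). No latest admission date is given.

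**The concern.** The denominator of the primary outcome is described by two rules in two paragraphs, one on discharge and one on admission, and the admission rule is introduced to deal with repeat admissions. A reader has to infer that it is also an eligibility limit.

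Even when the rules are combined, entry depends on when the patient leaves hospital. That happens after randomisation, and the intervention is meant to change it. Patients admitted and discharged within week one are excluded, while those admitted on the same days who stay longer are kept. At the other end, a patient still in hospital a month after the intervention ends is excluded. If stays differ between arms, these exclusions remove different patients from each arm, for readmission and for length of stay alike.

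The roster can act in the same direction. The intervention spans two physician rotations, so a patient discharged in the following month may carry the number of a physician who was not on the list. Such patients tend to have longer stays.

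**Working it through.** **1. The plan's own power.** Inputs from the Sample size and Randomization sections: 10 teams per arm, m = 200 per team, intracluster correlation 0.01, 10% versus 5%, significance 0.05 (taken as two-sided).

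- Design effect = 1 + (200 − 1) × 0.01 = 2.99.
- Effective n per arm = 2000 / 2.99 = 668.9.
- Power = Φ{[|p1 − p2| − 1.96√(2p̄(1 − p̄)/n)] / √([p1(1 − p1) + p2(1 − p2)]/n)}.
- With p̄ = 0.075: (0.05 − 1.96 × 0.01440) / 0.01434 = 1.52, so power = 93.6%, against 93% stated.
- The second statement, 5% versus 2.5%, gives 67.3% against 67% stated.

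Both figures reproduce.

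**2. Can the two rules stand together?** Yes: admitted during the roughly eight weeks and discharged from week one up to a month after the end. This is close to the population in the Sample size section, which counts admissions in the two-month period.

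**3. What the discharge-date rule drops under that joint reading.** Assume uniform admission over 56 days and exponential stays with mean L days. The documents give no figure, so L is varied from 4 to 14.

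- Admitted and discharged in week one: [7 − L(1 − e^(−7/L))]/56. For L = 4 this is 3.70/56 = 6.6%; for L = 14 it is 1.49/56 = 2.7%.
- Still in hospital one month (30.4 days) after the end: (L/56)(e^(−30.4/L) − e^(−86.4/L)). For L = 4 this is close to 0%; for L = 14 it is 2.8%.

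The counts are small, but both groups are chosen by length of stay.

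**4. What the roster could lose.** The share of admitted patients discharged after the end is (L/56)(1 − e^(−56/L)). Suppose, as a worst case, that all of them are unlinkable:

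| Mean stay (days) | Discharged after end | Patients left per team | Power |
|---|---|---|---|
| 4 | 7.1% | 186 | 93.0% |
| 6 | 10.7% | 179 | 92.7% |
| 8 | 14.3% | 171 | 92.3% |
| 10 | 17.8% | 164 | 91.9% |
| 14 | 24.5% | 151 | 91.1% |

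The largest loss is 93.6 − 91.1 = 2.5 points.

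**5. Drug-therapy window.** It closes between about one month (30.4 days) and two months (61 days) after the end. The part of the calendar window after the end is 4.34/(8 + 4.34) = 35% up to 8.71/(8 + 8.71) = 52%. The share of patients admitted after the end is lower than this, because some late discharges were admitted earlier.

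**6. The conditional case.** Suppose the first-admission sentence only removes duplicates, and patients admitted after the end have no effect at all.

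- Window = 7 + 4.33 = 11.33 weeks.
- Share admitted after the end, for a 7-day mean stay (assumed) = (4.33 − 1)/11.33 = 29%; for 4 to 10 days, 33% to 26%.
- Diluted effect = 5.0 × (1 − 0.29) = 3.5 points (3.3 to 3.7).
- Patients per team = 200 × 11.33/8.7 ≈ 261; design effect = 1 + 260 × 0.01 = 3.6; effective n per arm = 2610/3.6 = 725.
- Power = 69% (63% to 74%).

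**The case against.** A reader might infer that the discharge window contradicts the first-admission rule, mixes in unexposed patients, and so undoes the 93% power. The documents do not support that.

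- One rule concerns discharge and the other admission. Applied together they exclude patients first admitted before the start or after the end.
- The fall to about 69% needs the first-admission sentence to be read as de-duplication only, and the effect to be exactly zero after the end. The protocol states neither. It aims at a change in culture, and the intervention also reaches nurses and allied staff, who are not said to leave when physicians rotate.
- Dilution and roster loss cannot both apply in full, since a patient who cannot be linked to a team cannot dilute the contrast.

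A reader might also infer that physicians who change teams carry the wrong arm. Nothing says that the team assignments supplied are undated, and no movement between arms is documented.

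Two further points deserve weight. The extra month plausibly exists to capture late discharges, which is sensible. And the Readmission data section already excludes stays above the 99th percentile for Ontario hospitals, so some very long stays would go in any case.

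What these arguments do not answer is that selection still turns on discharge date, that the roster wording is inconsistent, and that the drug-therapy cohort really has no upper limit on admission.

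**Conclusion.** The point holds as a defect of definition that is cheap to repair. It does not show that the trial is underpowered: the 93% is correct for patients admitted during the intervention, and the joint reading gives nearly that population.

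What stands:

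1. The primary and length-of-stay cohorts are selected partly on length of stay. Under the assumed stay distribution this removes about 3% to 7% of admissions in week one, and up to about 3% at the far end.
2. On the narrower roster wording, 7% to 25% of admitted patients could be unlinkable. That costs at most about 2.5 points of power, but it removes longer stays selectively. The documents give no basis for sizing the resulting bias.
3. The drug-therapy cohort includes patients first admitted after the intervention ended.

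The 3.5-point contrast and 69% power show only what is at stake if the first-admission sentence is misread and the effect also stops at the end date. They are not a finding about the plan as written.

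**What to change.** - **Index rule.** Define the index as the first eligible general internal medicine admission with an admission date from the site's intervention start (or start plus one week, if a run-in is wanted) to its end date, followed to discharge whenever that occurs. A run-in set on admission date drops everyone admitted in that week alike, whatever their stay.
- **Scope.** Use this rule for readmission, length of stay and drug therapy, and state it once.
- **Roster.** Use one term for the period throughout Readmission data, and request team assignments with service dates running to the last eligible discharge at each site.

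The cost is protocol wording, a slightly longer roster request to the same division leaders, and fewer patients in the drug-therapy cohort. The primary sample stays essentially the one that the Sample size section already assumes.

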#### Length of stay

Mean lengths of stay will be compared between patients discharged from intervention and control group CTTs. Intervention group effects will be estimated with linear mixed models.

#### Collaboration survey data

Confirmatory factor analytic methods will be used to investigate scale structure and reliability of data. Intervention group effects will be estimated with linear mixed models. Secondary analyses will investigate stability and change (growth) in survey scores over time.

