### Objectives: hypotheses

The SCRIPT Programme aims to create a cultural shift in the way health professionals communicate and collaborate in GIM hospital teams. There are three objectives for the SCRIPT Programme, the first two of which have been successfully completed. They are:

1. To assess interprofessional communication and collaboration;

2. To create an intervention – a tool or other process – that improves interprofessional communication and collaboration;

3. To implement and evaluate the effects of the intervention on outcomes.

The objective of the trial is to implement and evaluate the effects of an intervention aimed at enhancing collaborative communication between professionals and improving patient-centred care.

The research hypotheses for trial-related quantitative outcomes are:

1. Patients who are discharged from intervention teams will be less likely to be readmitted to hospital than patients discharged from control teams;

2. Mean time to readmission will be longer for patients discharged from intervention teams than for patients discharged from control teams;

3. Patients who are cared for by intervention teams will have shorter mean lengths of stay than patients in control teams;

4. Survey-measured perceptions of interprofessional collaboration will be higher among staff members of intervention teams than staff members of control teams;

5. Patients will report higher satisfaction with care after being treated by intervention teams than by control teams;

6. There will be an association between the number of calls to staff members' paging devices and team status; intervention-team staff members will receive fewer pages;

7. Adherence rates to evidence-based best practices for prescription drug therapy of geriatric acute-care inpatients will be greater among intervention teams than control teams.

Qualitative data are not collected in confirmation or denial of a hypothesis, but in explanation of the findings of the intervention trial. These data will be used to understand staff perceptions of the effects of the intervention and the barriers and catalysts for its implementation.

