#### Collaboration survey data

The purpose of the survey is to measure staff members' perceptions of interprofessional collaboration. It is an adaptation of the Collaboration Among Medical Staff Subscale (CMSS) from the Nurses' Opinion Questionnaire [21] The CMSS measures professional working relationships among nurses, physicians, and other health care professionals. It was developed on a belief that the organizational structure, role behavior, and communication patterns and methods between caregivers affect patient outcomes and staff satisfaction. Validity and reliability of data from published versions of the CMSS have been acceptable [22,23].

We will administer an adaptation of the CMSS containing 28 question items, fourteen unique items presented twice on one page, with vocabulary changed slightly to reflect the two major groups of GIM staff with whom a respondent works. Physicians will respond to survey items that target nurses, allied health staff, and unregulated clerical and clinical support workers; nurses respond to survey items targeting physicians, allied health staff, and unregulated clerical and clinical support workers; and allied health staff respond to survey items targeting physicians, nurses, and unregulated clerical and clinical support workers. The survey will be coded so that higher scores will represent higher perceived importance and existence of interprofessional collaboration within the team.

We plan three administrations of the survey instrument. The first will occur as close as possible to the first day of intervention implementation in the GIM teams. The second administration will occur after full implementation of the study's interventions, about eight weeks later. The third will occur eight weeks after the second.

In randomized trials, data from participants who are unaware of the past group condition, treatment or control, can be valuable [24,25]. Accordingly, the third survey administration will have particularly strong potential to survey staff who joined their GIM division and CTT after the conclusion of the intervention, eight weeks post-intervention. We expect that these staff members will be naïve to the past group condition of the clinical teams with which they are presently working.

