#### Covariates

Model-based estimates of intervention effects on the outcomes of readmission, length of stay, use of optimal drug therapy, patient satisfaction, and use of paging devices will employ patient-level and team-level covariates. Patient-related factors to be controlled will be patients' age and gender.

Other covariates will be measures of hospital health care processes hypothesized to be related either to outcome measures or to intervention uptake. The intervention's focal concern is the improvement of interprofessional performance of GIM teaching teams. Therefore, we propose to use the following constructs as structural indicators of functional team processes of care:

• *Ward-based assignment of medical, nursing, and allied health professional staff*. 'Ward basing' refers to hospital practices specifying the deployment of healthcare staff members to a single physical ward location. This arrangement is in contrast to assignments that have staff members working among different medical teams or nursing units as they treat patients. For example, if nurses and nursing units are fixed to physical ward locations, then medical team and professional health staff members could be assigned to patients in such a way that they are required to work with members of several different nursing units. If so, they are said to 'cross teams or units.' On the other hand, if medical teams are fixed to physical ward locations, then it is possible that nurses and professional health staff could be required to work among multiple different medical teams. It is also possible that both medical teams and nursing units are given fixed assignments to single ward locations and professional health staff are assigned to work across multiple combinations of medical teams and nursing units. All of these configurations create variation in the degree to which GIM staff are consolidated to work in one physical location.

Work assignments that see GIM staff consistently – and as a matter of hospital policy – working in multiple physical locations, where work colleagues are more likely than not to be unfamiliar, might have negative impacts on achievement of effective interprofessional collaboration and patient outcomes. An indicator variable will be developed to code whether clinical teaching teams are organized to consolidate interprofessional teams and team members to a single physical ward location.

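### The staff-survey analysis names no respondent-profession term although the form differs by profession; adding one is a free, modest improvement for hypothesis 4

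*Protocol article*

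**What the plan says.** Objectives: hypotheses, item 4, treats staff as one group: "Survey-measured perceptions of interprofessional collaboration will be higher among staff members of intervention teams than staff members of control teams".

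Outcomes: measurement, Collaboration survey data, gives each profession its own version of the form:

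- Version for physicians: "Physicians will respond to survey items that target nurses, allied health staff, and unregulated clerical and clinical support workers".
- Version for nurses: "nurses respond to survey items targeting physicians, allied health staff, and unregulated clerical and clinical support workers".
- Version for allied health staff: "allied health staff respond to survey items targeting physicians, nurses, and unregulated clerical and clinical support workers".

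All versions use the same fourteen items with small changes of vocabulary, and one coding direction: "The survey will be coded so that higher scores will represent higher perceived importance and existence of interprofessional collaboration within the team". The same section adds that, at some sites, nurses and other health professionals who serve both arms pick for themselves the team they answer for.

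Statistical methods, Collaboration survey data, plans a confirmatory factor analysis and then states only: "Intervention group effects will be estimated with linear mixed models. Secondary analyses will investigate stability and change (growth) in survey scores over time".

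Statistical methods, Covariates, says which outcomes receive covariates. It begins with readmission and LOS, and the sentence ends: "use of optimal drug therapy, patient satisfaction, and use of paging devices will employ patient-level and team-level covariates". That is five of the six quantitative outcomes in the Abstract. The staff survey is the one left out.

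**The concern.** A respondent's profession determines whom the items are about. Nurses never rate nurses, and physicians never rate physicians. If mean scores differ by profession, a team's mean score depends partly on how many of each profession returned the form.

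The number and mix of respondents are not fixed by the design. An analysis that ignores profession therefore lets differences in mix between teams enter the comparison of 10 with 10 teams. At the least this adds noise. If the mix also differed systematically by arm, it would move the estimate itself. Profession is implied by the version of the form that a person completes, so the information is already to hand. What is at stake is the precision and interpretability of one secondary outcome.

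**Working it through.** The documents state no sample size, SD, intracluster correlation (ICC), response rate or profession mix for the survey, so there is no survey figure to reproduce. Every survey input below is an assumption. Only the layout comes from the protocol (Randomization, Sequence generation): five sites with four teams each, two per arm, so 10 v 10 teams.

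**1. Overlap of the targets.** All three professions rate support workers. Any two professions also share one further target: physicians and nurses share allied staff, physicians and allied staff share nurses, nurses and allied staff share physicians. The forms differ but are not unrelated.

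**2. Shift if the mix differs by arm.** Without a profession term:

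shift = (profession gap in mean score) × (arm difference in that profession's share of respondents)

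| Gap (SD) | 5 points | 10 points | 20 points | 30 points |
|---|---|---|---|---|
| 0.2 | 0.01 | 0.02 | 0.04 | 0.06 |
| 0.5 | 0.025 | 0.05 | 0.10 | 0.15 |
| 0.8 | 0.04 | 0.08 | 0.16 | 0.24 |

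A simulation agrees. Its assumptions were 20 respondents per team, team ICC 0.05, physicians about 35% of respondents with a between-team SD of 15 points, physicians 0.5 SD apart from the rest, true effect 0, and 150 runs per scenario. For expected arm differences of 0, 10 and 20 points in physician share, the mean estimate was -0.01, 0.05 and 0.10 SD without profession, and -0.01, 0.00 and 0.00 SD with it.

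**3. Precision when the mix is balanced in expectation.** With the same assumptions:

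- Variance of a team mean apart from mix: 0.05 + 0.95/20 = 0.0975.
- Variance of a team's realised physician share: 0.15² + (0.35 × 0.65 - 0.15²)/20 = 0.0225 + 0.01025 = 0.03275.
- Variance added to a team mean by mix: gap² × 0.03275.
- Share of variance removed by a profession term (ignoring the small cost of estimating it): gap² × 0.03275 / (0.0975 + gap² × 0.03275).

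At a gap of 0.3 this is 0.00295/0.10045 = 2.9%. At 0.5 it is 0.00819/0.10569 = 7.7%. The SD of the arm difference at a gap of 0.5 is √(0.2 × 0.10569) = 0.145 without profession and √(0.2 × 0.0975) = 0.140 with it. The simulation gave about 0.14 and 0.13, which agrees within its Monte Carlo error (0.145/√300 = 0.008).

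A second simulation used other assumptions: 25 respondents per team, ICC 0.05, an average physician/nurse/allied mix of 30/50/20, and nurse share varying between teams with an SD of 12-20 points. Adding profession cut the variance as follows:

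| Physician-nurse gap (SD) | Variance reduction |
|---|---|
| 0.3 | 3-5% |
| 0.5 | 4-8% |
| 0.8 | 13-19% |
| 1.0 | 19-30% |

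**4. Size of chance imbalance.** Under the step 3 assumptions the arm difference in physician share has SD √(0.2 × 0.03275) = 0.081, or about 8 points. At a gap of 0.5 SD that contributes 0.5 × 0.081 = 0.04 SD of random error.

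**The case against.** The strongest reply is that the text is silent and does not state a pooled model. The survey paragraph lists no model terms at all, not even team, site or wave, and an article may leave these to a fuller document. The covariates that the Covariates section assigns are patient-level and team-level. Respondent profession is neither, so the survey's absence from that list does not rule it out. This stands in part: nobody can say that profession is excluded. But the article does specify covariates at length, names five of six outcomes, and frames hypothesis 4 as one comparison of all staff. An unadjusted staff comparison is its most natural reading.

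A reader might go further and infer that the hypothesis 4 estimate is biased. The documents do not support that. Allocation of two teams to each arm within each site balances the mix in expectation, and under that condition the simulated estimate centred on zero. Rotation of medical staff replaces physicians with physicians and does not by itself change the profession mix. Self-selection of team applies only at some sites, and no figure shows that it differs by arm. Nor do the professions rate wholly different things: the items are the same and the targets overlap.

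It is also fair to say that the gain is small at moderate gaps, and that a 0.05 SD shift lies well below one standard error (about 0.14 SD under the same assumptions).

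**Conclusion.** The point holds as a free improvement on a secondary outcome, with moderate confidence. As stated, the plan does not account for respondent profession in the hypothesis 4 analysis, so the estimate depends partly on who answered in each team.

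The main consequence is chance imbalance and some lost precision: about 3-8% of the variance at profession gaps of 0.3-0.5 SD. Larger gains appear only with gaps of 0.8 SD or more, for which the documents give no support.

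Systematic bias is conditional. It would arise only if response, or the choice of team by staff who cross teams, differed by both arm and profession. All these magnitudes rest on assumed respondent numbers, ICC, gaps and mix. The primary readmission analysis is unaffected.

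**What to change.** In Statistical methods, Collaboration survey data, state that the survey linear mixed model includes respondent profession (physician, nurse, allied health) as a fixed effect, with team as the cluster. Report the arm difference by profession as supportive. Extend the confirmatory factor analysis already planned to check that the structure is comparable across the three versions of the form before their scores are combined.

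The cost is a change of wording and two respondent-level parameters. No new data are needed and no team-level degrees of freedom are used. A profession term does not correct self-selection of team within a profession, so that limitation remains.
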